### Ethical considerations

This trial has been approved by the Ethics Board of Clinical Research of Hospital Príncipe de Asturias (date May 26, 2011, OE 09/2011 CP 11/02132) and positively evaluated by the Comisión Central de Investigación de la Gerencia de Atención Primaria de Madrid (report dated March 23, 2011). The trial will fulfill the basic principles of the Helsinki Declaration (2008), Good Clinical Practice standards, and current Spanish legislation (Real Decreto 223/2004).

The researcher will properly inform the subjects who participate in the trial and written, informed consent will be requested, signed, and dated. Participants will be given oral and written, complete, and adequate information about the nature, purpose, and possible risks and benefits of their participation in the trial.

## Discussion

Systematic reviews of studies [14-17] evaluating the effectiveness of interventions and caregiving strategies for the caregiver show methodological limitations in their conclusions, mainly related to insufficient sample sizes, high losses to follow-up of subjects, and follow-up period duration. They also reveal the variability of the interventions and outcome variables employed.

The CuidaCare intervention is a personal intervention, aimed at both the caregiver and the dependent patient, and based on coping techniques.

The design selected for this project is the best possible given the intervention, while seeking to avoid possible contamination effects among centers. The number of clusters is sufficient for the randomization to balance potentially confounding factors among themselves and we consider modelization techniques which take into account the intracluster correlation.

Given the nature of the intervention, it cannot be masked. However, we have designed a blind evaluation of the outcome.

Subjects will be recruited for the study by their own nurses. This increases variability, which we attempt to minimize by training all participating nurses on the one hand, and by creating a research protocol and implementing an electronic data collection notebook on the other hand.

Of note, the fact that nurses recruit their own patients increases implementation in standard practice.

Participation of nurses is voluntary. We are aware that a bias is introduced, but they are motivated and engaged professionals who will facilitate the development of innovative interventions such as CuidaCare.

Despite loses to follow-up in primary care being minimal as a result of the user's proximity to the system and the possibilities the health professional has to contact relatives and friends, we have estimated a high percentage in the trial due to the high morbidity-mortality of dependent patients, which will force the caregiver to abandon the trial due to the patient's hospitalization or death.

The design of the trial is pragmatic, which will allow evaluating not only its effectiveness, but also its applicability in the context of primary care.

We consider that a structured, standardized intervention can improve the quality of life of older caregivers. Detailed information about the intervention, informal care, and dependency degree of the relative receiving care can contribute to understanding what types of strategies result in improvements to the quality of life of the caregiver, and to pay attention to relevant factors which allow for designing more specific and homogeneous care plans for this population.

Currently, studies on the effectiveness of nursing interventions are very limited in this field. This project can contribute to opening new research lines on nursing approaches to care problems of informal caregivers in primary care, help compare the effectiveness among different nursing interventions, and their associated cost-effectiveness analysis.

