### Studied subjects

Subjects ≥65 years, identified by the nurse as the main caregiver of a patient included in the home consultation service of the *Cartera de Servicios estandarizados de Atención Primaria *[23] at the moment of inclusion in the study.

The person who assumes responsibility for the support and daily care of the dependent patient is termed the main caregiver [8].

1. Inclusion criteria:

• Age ≥65 years.

• Caregivers who have been carrying out this function for >1 month.

• Time employed as main caregiver is >6 months per year (even during non consecutive months).

• Not currently under another therapeutic intervention to ease caregiver tension.

• Able to follow the specific requirements of the trial.

• Willing to participate in the trial and provide written consent.

2. Exclusion criteria:

• Main caregivers of institutionalized patients.

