### Sample size

Sample size has been calculated considering a relevant post-intervention average difference of 15 points between the intervention and control groups measured on the EQ-5D VAS, and a standard deviation of 25 (estimation obtained from Roset et al. [26]). This difference is equivalent to an effect size of 0.6.

Assuming an alpha error of 0.05 and a beta error of 20%, 44 caregivers are necessary for each group.

Since randomization is done by clusters, the sample size is adjusted in order to take into account the design effect. We have considered an intraclass correlation coefficient of 0.02 [27] and assumed an average cluster sample size of 15 caregivers. The design effect is 1.28. With these assumptions and expecting a 20% loss to follow-up after a 1-year period, the required sample size is 142 (71 caregivers per group).

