### Withdrawal criteria

Main caregivers who, once recruited, sicken of a severe pathology.

Main caregivers of dependent patients who are hospitalized for more than 3 months over the trial period.

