### Analysis

1. Descriptive analysis of each variable with its corresponding 95% confidence interval (CI). Tests for normality. Description of the profile of patients who abandon the study, and their reason for withdrawal.

2. Comparison of the group at the beginning of the trial for response variables, descriptive variables, and prediction factors. Bivariate, statistical, and other tests appropriate for the type of variable (qualitative or quantitative) will be used.

3. Analysis of primary outcome at the end of the intervention (0 month of follow-up period), and at 6 and 12 months after the intervention. The average change in EQ-5D VAS value before and after the intervention will be compared between the two groups by using parametric and/or non-parametric tests and the CI of the difference will be calculated. A mixed-effects regression model will be used to adjust by prognostic factors. Confounding factors or factors that may alter the recorded effect will be taken into account in this analysis.

4. Analysis of secondary outcome. For each of the secondary response variables, the variable outcomes will be compared based on the assigned group by calculating the difference of means or proportions of each variable, as well as CIs.

All statistical tests will be performed as intention-to-treat. The last and baseline observations carried forward will be used for missing data. Significance will be set at p < 0.05.

Researchers in charge of performing the analysis will not know which intervention has been assigned to each of the included patients.

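### Withdrawal criteria and Discussion disagree on whether a patient's death ends the caregiver's participation, and so on whether an observed or a carried-forward VAS enters the analysis

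*Protocol article*

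**What the plan says.** The section on withdrawal criteria in the protocol article has two entries. One concerns the caregiver: "Main caregivers who, once recruited, sicken of a severe pathology". The other concerns the patient: "Main caregivers of dependent patients who are hospitalized for more than 3 months over the trial period". Death of the patient is not listed.

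The Discussion gives as its reason for a high loss estimate the "high morbidity-mortality of dependent patients, which will force the caregiver to abandon the trial". The clause in full names the two events: "which will force the caregiver to abandon the trial due to the patient's hospitalization or death". It gives no minimum length of hospitalisation, and it names death.

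The sample size section builds in the corresponding allowance, "expecting a 20% loss to follow-up after a 1-year period". The Analysis section states that "All statistical tests will be performed as intention-to-treat" and that missing values are replaced by the last or the baseline observation. The primary outcome is the caregiver's own rating on the EQ-5D VAS, collected at baseline, at the end of the 6-month intervention, and 6 and 12 months after that.

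**The concern.** If a dependent patient dies during the trial, the article gives two answers on whether the caregiver is still followed. Under the withdrawal criteria nothing has happened that ends participation, and the VAS is collected at the next visit. Under the Discussion the caregiver leaves, and later VAS values are missing.

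The event is not a rare one for this trial: the Discussion offers it, with hospitalisation, as the reason why the loss estimate is high when losses in primary care are usually small. Nor does it stop measurement, since the caregiver rates his or her own health and can do so after the patient has died or been admitted. At stake is how much of the primary outcome is observed and how much is filled in by carry-forward, in the very group that the trial expects to lose.

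**Working it through.** **1. The two sections side by side**

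| Event | Withdrawal criteria | Discussion |
|---|---|---|
| Patient dies | Not a criterion | Caregiver leaves |
| Patient hospitalised more than 3 months | Withdrawn | Caregiver leaves |
| Patient hospitalised 3 months or less | Not a criterion | Caregiver leaves, if read literally |
| Caregiver falls seriously ill | Withdrawn | Not mentioned |

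Death is a clear conflict. The withdrawal criteria contain no rule on death that the Discussion could be abbreviating. Short hospitalisation is a possible conflict only, because the Discussion may be abbreviating the 3-month rule.

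**2. The plan's own figure**

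Inputs from the sample size section: difference 15, SD 25, alpha 0.05 (two-sided reproduces the figure), power 80%, ICC 0.02, cluster size 15, loss 20%.

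- Per group: 2 × (1.96 + 0.842)² × (25/15)² = 43.6, rounded up to 44.
- Design effect: 1 + (15 − 1) × 0.02 = 1.28, and 44 × 1.28 = 56.32.
- Loss: 56.32 / (1 − 0.20) = 70.4, rounded up to 71 per group, 142 in all.

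The stated 142 is reproduced. This point does not change it.

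**3. How many caregivers**

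0.20 × 142 = 28.4, or 14.2 per arm. This is a ceiling for patient events, since the article gives no split by cause and caregiver illness is a separate listed reason.

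**4. What happens to them in the analysis**

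The Analysis section keeps them by intention-to-treat with a carried value. If the patient dies before the end-of-intervention visit, the caregiver has only a baseline VAS, so the carried change is zero. If the patient dies later, the last post-intervention value is carried.

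**5. Illustration of the cost of carry-forward**

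Assumptions: a share d of both arms carries forward zero change, the SD stays at 25, and the design effect is 1.28. Loss rates other than 20% are also assumed.

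Power = Φ[δ / (25 × √(2/n)) − 1.96], with n the effective number per arm.

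- As the sample size plans it (20% lost, 15 points in the rest): n = 71 × 0.80 / 1.28 = 44.4; SE = 5.31; 15/5.31 = 2.83; power = Φ(0.87) = 0.807.
- All 71 kept, 20% at zero change: δ = 15 × 0.80 = 12; n = 71 / 1.28 = 55.5; SE = 4.75; 12/4.75 = 2.53; power = Φ(0.57) = 0.715.

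| Share d | Power, leavers lost | Difference with zero change carried | Power, zero change carried |
|---|---|---|---|
| 10% | 0.850 | 13.5 | 0.812 |
| 20% | 0.807 | 12.0 | 0.715 |
| 30% | 0.753 | 10.5 | 0.599 |

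The sample size thus allows for leavers as lost numbers, whereas the Analysis section keeps them with imputed values.

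**The case against.** The strongest reply is that the withdrawal criteria are the operative text and the Discussion is a remark on why a high loss was assumed. A caregiver may also leave of his or her own accord after a bereavement, which is an abandonment and not a protocol withdrawal. For hospitalisation this reply has force. For death it does not remove the conflict: the Discussion says that the event forces the caregiver out, and the only formal list gives no ground for that.

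Several stronger readings are tempting, and the article does not support them.

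- A reader might infer that nurses who know the arm decide who is withdrawn. No section names the decision-maker, and the section on masking has post-intervention measurements made by nurses unaware of the group.
- A reader might infer that the conflict decides who is in the analysis. The Analysis section keeps leavers, with carried values; what varies is observed against imputed data.
- A reader might go on to estimate a bias from one arm keeping these caregivers while the other deletes them. The plan states no deletion, and nothing shows that the arms would act differently.
- A reader might see a further contradiction in the exclusion of "Main caregivers of institutionalized patients". That is an entry criterion. The article is silent on a later move to an institution, and silence in a condensed article is not a contradiction.

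**Conclusion.** The point holds in a limited form. The two sections conflict on patient death and may conflict on hospitalisation of 3 months or less. The group concerned is at most about 28 of 142 caregivers, and the conflict leaves open whether their later VAS is measured or carried forward.

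The fall from 15 to 12 points, and from about 0.81 to 0.72 in power, illustrates the possible cost of carry-forward and is not a forecast. It takes the whole 20% loss as carried at zero change in both arms. Events after the end-of-intervention visit would carry a later value, and zero changes would also alter the SD. Nor would continued measurement necessarily restore 15 points, since the effect in bereaved caregivers is unknown. It would put data in place of an assumption, which fits the stated intention-to-treat analysis. The sample size of 142 stands.

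**What to change.** Reconcile the withdrawal criteria with the Discussion on patient death, and make clear whether the Discussion means any hospitalisation or only that beyond 3 months.

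State that neither ending the intervention nor meeting a withdrawal criterion (patient death, if it is made one, patient hospitalisation or caregiver illness) ends outcome follow-up. Collect the EQ-5D VAS at 0, 6 and 12 months after the intervention, in both arms, from every caregiver who still consents and is able to answer. Record the event and its date. Carry values forward only where the VAS truly cannot be obtained. Whether intervention visits continue after such an event is a separate matter for the sponsor to reconcile.

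The cost is a change of wording and the remaining assessments of at most about 28 caregivers, at visits already scheduled. The downside is some added variability in the VAS from bereaved caregivers.

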## Abbreviations

BADL: Basic activities of daily living; CI: Confidence interval; EQ-5D: EuroQol-5D; HRQL: Health-related quality of life; PHCC: Primary health care center; NANDA-I: North American Nursing Diagnosis Association-International; NIC: Nursing interventions classification; NOC: Nursing outcomes classification; VAS: Visual analogue scale.
